### Methods in analysis to handle protocol non-adherence and any statistical methods to handle missing data {20c}

Multiple imputation will be used to address missing data for intention-to-treat (ITT) analyses, as ITT prevents biases in the treatment effect [27]. Specifically, multiple imputation by chained equations will be applied under the assumption that data are missing at random. The imputation model will include baseline scores, group assignment, and other relevant predictors of missingness. In addition to the ITT analyses, exploratory per-protocol analyses may be conducted to gain further insight into the effects among participants who completed the study as intended.

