#### Primary outcomes targeting smoking behavior

Changes in tobacco dependency over time are operationalized as follows:Mean score changes in the"Fagerström Test for Nicotine Dependence"[20],German version: [9].Mean score changes in the “Alcohol, Smoking, and Substance Involvement Screening Test” (ASSIST) subscale for tobacco [58].Mean score changes in the measured carbon monoxide (CO) level in exhaled breath using the Smokerlyzer®, additionally assessed during each session of the intervention.

Changes in smoking status over time are operationalized as follows:d.Changes in the proportion of positive versus negative results in self-administered urine tests measuring cotinine content, using a dichotomous outcome (positive/negative; cutoff 200 ng/ml; for an overview, see [8]).

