### Sample size {14}

To estimate the required sample size, an a priori power analysis was conducted using G*Power 3.1.9.7 [21]. The primary hypothesis will be tested using a 2 × 4 mixed-design repeated-measures ANOVA (with a power of 1 − *β* = 0.80 and a significance level of *α* = 0.05. This requires a sample size of approximately 62 participants in total, 31 per condition, to detect a moderate effect. No additional participants will be recruited to compensate for potential dropout; instead, the study design follows the intention-to-treat (ITT) principle and employs multiple imputation methods to address missing data. The decision to target a moderate effect size is driven by practical considerations to detect treatment effects that are both statistically significant and practically meaningful.

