## Statistical methods

### Statistical methods for primary and secondary outcomes {20a}

Treatment effects on the continuous primary outcomes (i.e., tobacco dependence, smoking intensity, mental health symptoms) will be tested by computing mixed 2 (condition) × 4 (time) analyses of variance (ANOVAs) for repeated measurements for each applied outcome variable. To reduce the likelihood of Type I errors due to multiple comparisons, the false discovery rate (FDR) will be controlled using the Benjamini-Hochberg procedure [7] across the primary outcome measures. In the case of potential violations of the sphericity assumption, the Greenhouse–Geisser method will be applied.

It will be examined whether the experimental condition leads to higher abstinence rates at post- and follow-up assessments using chi-squared tests.

Secondary and exploratory analyses testing for potential mediating variables will be conducted using regression analyses or structural equation modeling. Treatment effects on the AAT will be tested by computing mixed 2 (condition) × 4 (picture category) analyses of variance.

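### One missing-at-random imputation covers the primary abstinence result; if relapse-related dropout is heavier in the treated arm, it overstates the benefit and can make it significant

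*Protocol article*

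**What the plan says.** The section on missing data {20c} sets one approach: "Multiple imputation will be used to address missing data for intention-to-treat (ITT) analyses". It then says that "multiple imputation by chained equations will be applied under the assumption that data are missing at random". The model is described only in outline: "The imputation model will include baseline scores, group assignment, and other relevant predictors of missingness". The one other analysis mentioned there is optional: "exploratory per-protocol analyses may be conducted".

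Cotinine status is a primary outcome, defined "using a dichotomous outcome (positive/negative; cutoff 200 ng/ml" in the section on primary smoking outcomes. The statistical methods section {20a} tests whether the programme gives "higher abstinence rates at post- and follow-up assessments using chi-squared tests". No different missing-data rule is given for it.

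The sample size section {14} leans on the imputation: "No additional participants will be recruited to compensate for potential dropout", because intention-to-treat with multiple imputation is to deal with the losses.

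**The concern.** Missing at random means that, given what the imputation model contains, a patient whose test is missing is as likely to be abstinent as a similar patient who was tested. For abstinence in this design that is doubtful. Relapse is the outcome itself and may be why a patient stays away from a test. Nobody is blinded. One arm has been through six sessions in three weeks; the other is waiting for treatment promised after 6 months. The last assessment is 6 months after post-treatment, which leaves time for relapse that no visit records.

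If treated patients who relapse unseen stay away more than control smokers do, some are imputed as abstinent. With 31 per arm, a few such patients can decide the test on the most direct measure of whether the programme works. The optional per-protocol analysis does not address this, because it leaves out the patients in question.

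**Working it through.** **The plan's own figure.** The article gives 62 patients (31 per arm) for a 2 × 4 mixed ANOVA, power 0.80, alpha 0.05 and a moderate effect. Taking f = 0.25 (assumed; no value is given) for the group-by-time interaction, with λ = f²(N − 2)(4 − 1), N = 62 gives λ = 0.0625 × 60 × 3 = 11.25 and power 0.804. So 31 per arm is used below. The figure contains no dropout allowance.

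**Inputs.** From the document: 31 per arm, 1:1 allocation, chi-squared test, missing at random. Assumed: all abstinence and dropout rates.

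**Step 1: one example.** Treated: 21 seen, 9 abstinent, 10 missing. Control: 28 seen, 4 abstinent, 3 missing. Uncorrected Pearson: χ² = (p₁ − p₂)² / [p(1 − p)(1/n₁ + 1/n₂)], with p the pooled proportion.

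- Observed cases: 0.429 v 0.143, p = 13/49 = 0.265; χ² = 5.03, p = 0.025.
- Missing at random, imputed within arm and pooled by Rubin's rules: about 10 × 9/21 = 4.3 of the missing treated patients and 3 × 4/28 = 0.4 of the missing controls count as abstinent; p = 0.029.
- Missing = smoking: 9/31 v 4/31, p = 13/62 = 0.210; χ² = 2.43, p = 0.119.

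For the tipping point, hold control at 4/31 and treat counts as observed. Then 10/31 gives p = 0.068 and 11/31 gives p = 0.038. Nominal significance turns on whether two of the ten missing treated patients are counted as abstinent.

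A second example, 8/21 v 3/28 seen, gives p = 0.028 under missing at random and p = 0.097 for 8/31 v 3/31.

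**Step 2: bias when there is no effect.** Let a be true abstinence in both arms and s the share of treated smokers lost, with all treated abstainers attending and control losing 10% regardless of status. Imputing within arm, the expected spurious difference is a / [a + (1 − a)(1 − s)] − a. For a = 0.15 and s = 0.40: 0.15/0.66 − 0.15 = 0.077.

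Simulation, 4,000 trials per row; chance of a significant result favouring treatment, nominal 2.5%:

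| a, both arms | Treated smokers lost | Mean spurious difference, missing at random | Significant, missing at random | Significant, missing = smoking |
|---|---|---|---|---|
| 15% | 30% | 5.5 points | 6.7% | 4.4% |
| 15% | 40% | 7.8 points | 7.9% | 3.5% |
| 15% | 50% | 11.7 points | 13.7% | 4.3% |
| 15% | 60% | 16.5 points | 20.3% | 4.2% |
| 25% | 40% | 10.6 points | 11.7% | 4.5% |
| 25% | 50% | 14.7 points | 18.3% | 3.7% |

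Missing = smoking lies slightly above 2.5% here because it counts the lost control abstainers as smokers.

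**Step 3: a real effect.** True 25% v 10%, 40% of treated smokers lost: expected estimate 0.25/(0.25 + 0.75 × 0.60) − 0.10 = 0.257, about 26 points instead of 15. Significance in 58% of trials, against 35% with complete data.

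**Step 4: counter-checks at 15% in both arms.** Smoker dropout of 30% in both arms: 2.5%. Dropout unrelated to smoking, 30% treated v 10% control: 2.3%. Neither is inflated. (With a true 25% v 10% and equal 30% smoker dropout, the estimate widens from 15 to 18 points, but significance is no more frequent: 33% v 35%.)

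**The case against.** **It is an omission that a statistical analysis plan may fill.** That plan is not shown, and nothing in {20c} forbids further analyses. A reader might infer that abstinence will be analysed only under missing at random; the document does not say so. What stands is narrower: the article does not leave missing data open. It fixes one assumption for a primary outcome where that assumption is weakest, and relies on it in place of a dropout allowance.

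**Imputation need not use the completers' rate.** A reader might infer that every missing treated patient is imputed at the rate of those seen. That holds only if arm is the sole predictor. Baseline scores enter, and so do unspecified predictors of missingness. CO is measured at every intervention session, and cotinine, CO, FTND and ASSIST at four time points. If these values enter, relapse seen before dropout is largely handled. The simulations use no covariates and so show the unfavourable case. Relapse after the last visit remains.

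**The size is easily overstated.** At assumed completer rates of 35% v 10%, treating all 31 per arm as observed gives p = 0.018, which ignores imputation uncertainty. Testing only observed patients as a stand-in gives 0.028, 0.032 and 0.037 at 20%, 30% and 40% treated dropout (10% control). Missing = smoking gives 0.054, 0.102 and 0.186. Benjamini-Hochberg also applies across the primary outcomes. If the family is the eight listed, p = 0.029 meets its own threshold only from the fifth smallest onward (5 × 0.05/8 = 0.031), unless a larger p-value meets its own.

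**The direction is not documented.** Reminder calls are planned, and the promised later treatment could affect control retention either way. If control smokers leave more, the bias runs against treatment.

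**Missing = smoking is also an assumption.** With dropout of 30% v 10% unrelated to smoking it is biased against treatment (1.4% against a nominal 2.5%). This is why it should not replace the primary method or override it.

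**Conclusion.** The point holds conditionally. Missing-at-random imputation, as stated for every outcome, can overstate the abstinence difference and turn a non-significant comparison significant at 31 per arm (p about 0.03 against 0.12 in the worked example). With no true effect and 30% to 60% of treated smokers lost, the false-positive rate rises from 2.5% to between 6.7% and 20.3% at 15% abstinence.

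This rests on three assumptions: dropout depends on smoking; it does so more strongly in the treated arm; and the relapse is not captured by values in the imputation model. The design makes the first two plausible, but no dropout figure supports them. The p-values are before Benjamini-Hochberg.

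The documents do not support a claim that this trial's abstinence result will be biased, or that multiple imputation is the wrong primary method. Nor does any figure here support extending the point to the continuous outcomes.

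**What to change.** Amend {20c} before results are known; the article gives an amendment route, and data collection runs to April 2027.

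1. Keep multiple imputation as the primary analysis.
2. Name earlier cotinine, CO (including in-session readings) and FTND values as predictors in the imputation model.
3. Pre-specify, for cotinine abstinence, a sensitivity analysis in which a missing result counts as positive (smoking).
4. Preferably add an arm-specific tipping-point analysis: vary the assumed abstinence among missing patients separately by arm, and report where the conclusion changes.
5. Report these beside the primary result and temper the abstinence conclusion if they disagree, without giving missing = smoking a veto.

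The cost is a few sentences, a little more analysis and possibly a more cautious abstinence conclusion. No additional patients or visits are needed.

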### Plans to give access to the full protocol, participant-level data, and statistical code {31c}

The full study protocol, statistical code, and dataset will be available from the corresponding author upon request.

## Oversight and monitoring

### Composition of the coordinating centre and trial steering committee {5d}

The trial is coordinated by the core author group, consisting of the corresponding author and co-authors. Three student research assistants provide support for day-to-day tasks, including participant communication, administrative duties, and data maintenance. The core author group will meet weekly to oversee the trial process. During these meetings, the core author group will discuss the study progress, address challenges, and ensure smooth trial conduct. On a quarterly basis, a current status report will be submitted to the relevant stakeholder group, detailing the status of the project, its progress, and any problems that might have arisen. The stakeholder group comprises ten licensed psychotherapists who do not conduct the smoking cessation. As confirmed through the University of Siegen’s Ethics committee, the trial can be defined as moderate scale and of low-risk nature. Therefore, it was decided not to form a formal Trial Steering Committee. The trial is funded by the University of Siegen’s research unit; there is no other funding party involved.

As part of Patient and Public Involvement, psychotherapists actively address patients'willingness to participate in the study as part of routine care, ensuring that the study design aligns with participants'interests and preferences from the outset. Prior to the study, some patients had expressed a desire for greater support in achieving smoking abstinence within psychotherapeutic care, which was incorporated into the study concept to increase acceptability and relevance. Additionally, participants are encouraged to provide feedback throughout the study, as part of the Patient and Public Involvement process.

### Composition of the data monitoring committee, its role and reporting structure {21a}

No data monitoring committee has been deemed necessary, as this trial is classified as a low-risk intervention.

### Adverse event reporting and harms {22}

Nicotine withdrawal associated with smoking cessation can, in some cases, lead to increased irritability, sleep disturbances, concentration problems, or heightened feelings of hunger. These withdrawal symptoms typically occur in the first few days after smoking cessation and usually subside within 2 to 3 weeks [16]. These topics will be discussed during the smoking cessation program (sessions 1 and 2), and management strategies will be collaboratively developed for and with the patients. For example, relaxation exercises to cope with irritability, adopting sleep hygiene practices, or providing alternatives to manage increased hunger, such as drinking water, consuming sugar-free gum, or engaging in physical activity, will be addressed. No additional mental strains beyond those typical of quitting smoking are expected as a result of the study. Patients who report adverse events will have the option to undergo evaluation by the research staff and a psychotherapist. Oversight of safety, protocol adherence, study quality, and ethical conduct will be the responsibility of the study coordination unit.

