### Trial design {8}

The present research project demonstrates a single-center randomized controlled trial examining the impact of an intensive smoking cessation treatment compared to a waiting control condition on tobacco dependence and mental health symptoms related to the primary mental disorder among smokers aiming to initiate outpatient psychotherapy. All participants included in the study are receiving three psychotherapeutic consultations and fulfill an indication for psychotherapy. We chose to include a waiting control condition instead of an active (unspecific) control condition for comparison as a waiting control condition mirrors the typical course for patients awaiting psychotherapy, making the findings more applicable to real-world clinical settings. Eligible participants will be randomly assigned to either the experimental condition (immediate diagnostic session, a six-session smoking cessation program and a self-guided digital health application) or the waiting control condition (diagnostic sessions only). Patients randomly assigned to the control condition will be placed on a wait-list and will receive the smoking cessation intervention after 6 months. Post-treatment assessments for the intervention group will occur three weeks after their initial diagnostic session, which marks the end of the treatment phase. Similarly, participants in the control condition will undergo post assessments 3 weeks after their initial diagnostic session. Follow-up assessments for both groups will take place at 6 weeks (follow-up 1) and 6 months (follow-up 2) after the completion of the post-treatment assessments.

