Additionally, personalized recommendations tailored to each individual’s smoking behavior will be provided. Detailed descriptions of the individual sessions are outlined in the manual by Batra and Buchkremer [4]. In this research project, we will augment the original program by increasing session frequency and incorporating a self-help smoking cessation smartphone application to address specific challenges faced by smokers with mental disorders. While the original program was designed with weekly sessions over a course of 6 weeks, our intensified version will include two sessions per week, shortening the intervention duration to three weeks. Furthermore, participants will have access to the digital health application (*NichtraucherHelden®*,Sanero Medical GmbH, Stuttgart, Germany), a CBT-based self-help app featuring eight modules of psychoeducation, tasks, and relapse prevention. Recent evidence from a nationwide, multicentric, parallel, randomized controlled trial demonstrated the app’s feasibility and efficacy, with the intervention condition showing twice the abstinence rates at a 7-day point prevalence compared to the control condition [54].

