### Criteria for discontinuing or modifying allocated interventions {11b}

The assigned intervention can be terminated upon the patient's request, and participants may withdraw from the study for any reason. Researchers retain the authority to discontinue a patient's participation in the study if their mental health condition worsens, such as through experiencing a psychotic episode, exhibiting an acute increase in suicide risk, or an indication for hospitalization.

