### Participant timeline {13}

Smoking patients who have had three psychotherapeutic consultations at the Psychotherapeutic Outpatient Center of the University of Siegen will be informed about the option of participation in the current study. Interested participants will be contacted by the study team and undergo a telephone interview to determine eligibility and fulfillment of the inclusion criteria (*− t*_1_). Following telephone screening for a duration of 10–30 min, patients will be invited to the first smoking cessation session, during which informed consent will be obtained and psychological symptoms will be assessed within the course of a diagnostic session (baseline, *t*_*0*_). After the diagnostic session, during which all baseline measures will be assessed, patients will be randomly assigned either to the experimental group or the passive control group. The experimental condition will receive a 6-step smoking cessation program and additional access to a smartphone-based self-help application. The duration of the intervention will be three weeks. Afterwards, patients will be invited again to assess all measures of interest (*t*_1_). Six weeks (*t*_2_) and 6 months (*t*_3_) after completion, patients will be invited once again for follow-up assessments. The participants’ timelines and data assessment points are shown in Table 2..

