### Interim analyses {21b}

No interim analyses or formal stopping rules are planned for this study. The decision is based on the low-risk nature of the intervention, which involves behavioral support without invasive procedures or pharmacological treatments. Additionally, given the naturalistic design, we decided not to conduct interim analyses as they might compromise the integrity of the final data analysis. However, we remain attentive to participant safety and feedback. If any adverse events are reported or significant concerns are raised during participant evaluations (as part of Patient and Public Involvement), appropriate steps, including potential study termination, will be considered and documented accordingly.

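### Adverse events are stated to enter through patient report, with far more contacts in the treated arm before t1 and no stated link to the grave events in the discontinuation criteria

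*Protocol article*

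**What the plan says.** All of this is in the protocol article.

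- **Adverse event reporting and harms {22}:** "Patients who report adverse events will have the option to undergo evaluation by the research staff and a psychotherapist". The section expects irritability, sleep disturbance, poor concentration and hunger after quitting, and has them discussed in sessions 1 and 2. It describes no scheduled enquiry in either arm.
- **Trial design {8}:** the experimental arm receives "immediate diagnostic session, a six-session smoking cessation program and a self-guided digital health application". Controls have diagnostic sessions alone until they are offered the programme after 6 months.
- **Intervention description {11a}:** "our intensified version will include two sessions per week, shortening the intervention duration to three weeks".
- **Strategies to improve adherence {11c}:** a note after each programme session records departures from the manual and anything else of note.
- **Criteria for discontinuing {11b}:** researchers may end participation if mental health worsens, "such as through experiencing a psychotic episode, exhibiting an acute increase in suicide risk, or an indication for hospitalization".
- **Interim analyses {21b}:** "If any adverse events are reported or significant concerns are raised during participant evaluations", suitable steps, possibly including ending the study, will be considered.
- **Blinding {17a}:** none.

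**The concern.** Three sections each state a safety rule, and the rules do not meet. The harms section relies on the patient to speak up. The discontinuation criteria name the gravest events but do not call them adverse events. The interim-analysis section bases its study-level review on reported adverse events and on concerns raised in participant evaluations, without saying whether the discontinuation events are among them.

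The opportunity to report also differs by arm. A treated patient with poor sleep sees a psychologist twice a week and has been told to expect such complaints. A control with the same complaint has one visit in the same three weeks and no such prompt. Without blinding, nothing offsets this.

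The Discussion proposes that cessation could become part of standard psychotherapeutic care. Anyone weighing that will want to know how harms compared between arms, and data collected this way could not answer. There is neither a data monitoring committee nor a formal steering committee, so it matters what reaches the one stated study-level review.

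**Working it through.** **Contacts, counted from the protocol**

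- Programme sessions: 2 per week × 3 weeks = 6, which agrees with the six sessions stated.
- Treated, randomisation to t1: 6 sessions + t1 = 7. Participant timeline {13} says "patients will be invited to the first smoking cessation session, during which informed consent will be obtained", and randomisation follows that visit. If it is session 1, the count is 5 + 1 = 6.
- Control, randomisation to t1: t1 only = 1.
- Both arms then have t2 and t3. To t3: 7 + 2 = 9 (or 6 + 2 = 8) against 1 + 2 = 3. The 3 assumes that controls start the programme after t3.
- Reminder calls before follow-ups {18b} concern the date and adherence and are planned for both arms. They are not counted.

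**Effect on what is recorded**

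The protocol gives no adverse-event rate and no reporting probability, so these are assumptions. Let a share π of patients in each arm have a persisting complaint, volunteered with probability p at each contact, independently. With k contacts,

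recorded proportion = π × [1 − (1 − p)^k].

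π cancels from the ratio between arms.

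| Window | k treated vs control | p = 0.1 | p = 0.3 |
|---|---|---|---|
| To t1 | 7 vs 1 | 0.522 / 0.100 = 5.2 | 0.918 / 0.300 = 3.1 |
| To t1 | 6 vs 1 | 0.469 / 0.100 = 4.7 | 0.882 / 0.300 = 2.9 |
| To t3 | 9 vs 3 | 0.613 / 0.271 = 2.3 | 0.960 / 0.657 = 1.5 |
| To t3 | 8 vs 3 | 0.570 / 0.271 = 2.1 | 0.942 / 0.657 = 1.4 |

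For example, with π = 0.30 and 7 vs 1 contacts, the recorded proportions to t1 are 0.30 × 0.522 = 16% against 0.30 × 0.1 = 3% (p = 0.1), and 0.30 × 0.918 = 28% against 0.30 × 0.3 = 9% (p = 0.3). The true proportion is 30% in both arms.

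**Sensitivity to persistence**

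A complaint that begins only during the cessation phase (sessions 3 and 4 in Table 1) cannot be reported at every session. If only sessions 4, 5, 6 and t1 count, k = 4. The ratio is then (1 − 0.9⁴) / 0.1 = 0.344 / 0.1 = 3.4 at p = 0.1, and (1 − 0.7⁴) / 0.3 = 0.760 / 0.3 = 2.5 at p = 0.3. The direction is unchanged.

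**With equal enquiry**

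If both arms are asked the same questions at the same visits, k is equal and the ratio under equal true risk is 1.0.

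**The case against.** Three stronger readings are tempting, and the document does not support them.

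- **That adverse events count only if volunteered.** The harms section does not say so. It says what is offered to patients who report. Staff also write session notes, weekly meetings document issues {23}, and researchers may act on deterioration they notice {11b}. What stands is that patient report is the only route stated for adverse events as such. The session notes are themselves one-sided, and the meeting log is not described as an adverse-event record.
- **That a planned comparison of harms is biased.** No section plans one. The bias is a risk for any later harms table, not a fault in a stated analysis.
- **That the study-level review fires on trivial complaints and ignores grave events.** The review is discretionary, has no count or contrast between arms, and has a second limb for significant concerns. Nothing excludes a hospitalisation from it. What stands is that the discontinuation events are not stated to reach it, and that the second limb is tied to participant feedback.

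It can also be said that event definitions and forms belong in the full protocol, which the article says is available on request and which is not shown. That is fair for definitions and forms and limits the weight of the point. It does not remove the unequal contact, which follows from the stated design.

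Both arms complete the BDI-II and the 53-symptom BSCL at every assessment, so worsening of symptoms can be seen on equal terms. These are planned as mean changes in efficacy outcomes, however, not as a record of events.

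Finally, the model above assumes independent reporting of a persisting complaint, and the t1 window is the least favourable one. Hence the t3 rows and the sensitivity check.

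**Conclusion.** The point holds as a weakness of method with an inexpensive remedy. It does not threaten the efficacy analysis. The contact counts come from the protocol. That recorded harms would lean towards the treated arm follows from those counts if reporting is passive and equally likely at each contact. The amount of bias does not follow from the document: it rests wholly on the assumed 0.1 to 0.3 per contact, on equal true risk, and on a persisting complaint. The imbalance narrows after t1. Separately, the sections on discontinuation, interim analyses and harms leave open whether a psychotic episode, an acute rise in suicide risk or an indication for hospitalisation is recorded as an adverse event and considered at study level.

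**What to change.** 1. At t1, t2 and t3, add the same short fixed checklist to the digital questionnaires in both arms, covering the time since the last visit. It should list the withdrawal symptoms named in the harms section and the three events named in the discontinuation criteria, and end with an open question.
2. Base any summary of harms by arm on this checklist. List reports from session notes separately.
3. Record the events in the discontinuation criteria as adverse events, by arm, whoever detects them. Include them in the quarterly report that already goes to the group of psychotherapists who do not deliver the programme {5d}.
4. Reconcile sections {11b}, {21b} and {22} on which events feed the study-level review, without narrowing what can prompt it now.

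**Cost:** a few minutes per visit, some protocol wording through the amendment route in {25}, and more minor events recorded in controls. Data collection began in August 2024, so visits held before the change will lack the checklist. The date of the change should be reported, and earlier visits shown separately.
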